### Randomization and masking

The randomization sequence will be generated by SPSS 19.0 package (SPSS, Chicago, IL). The sequence will be password-protected and kept in a computer by [name]. Group allocation will be simple randomization in a ratio of 1:1 to either active treatment group or placebo group. The number sequences will be kept in sealed opaque envelopes and distributed to assessors. Patients, investigators and all sponsoring parties will be masked to treatment allocation until the end of the study. When there is a serious adverse event, the event will be discussed between the principal investigator Chinese medicine expert [name], and the co-investigator neurology specialist [name] to consider unblinding.

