### Primary outcome and its assessment

A positive primary outcome of this study will be an increase of at least four points in the Alzheimer’s Disease Assessment Scale-cognitive subscale (ADAD-cog) [27] total score; this is considered to be a clinically meaningful increase [28]. Total scores of the ADAD-cog, Chinese version of Mini-Mental State Examination (C-MMSE) [29,30] and Chinese version of Disability assessment for dementia (C-DAD) score [31] will be used as secondary outcomes.

Outcome measurements will be carried out during the study visits at weeks 0, 12 (half of treatment), 24 (end of treatment) and 30 (end of observation period). Safety assessment, which includes reporting of adverse events (AEs), measurement of vital signs and physical examination, will be carried out throughout the study. In addition, laboratory safety screening of liver and renal function will be performed at week 24. Bilingual assessors, trained by the same neurology specialist [name] and clinical psychologist [name], will be blind to the treatment allocation.

Clinical assessment will be rescheduled within 7 days after the scheduled clinical visit in case of any unexpected condition such as severe weather conditions. Phone call reminders will be given to the caregivers one day before the days of assessment.

A home diary will be given to each study participant’s caregiver to record treatment and changes in the participant’s medical condition. Formal instruction for the home diary will be given during the first visit. Revision and checking of the diary will be carried out with the caregiver during each formal visit by the assessors. Compliance in taking the treatments will be determined by the record of the diary and the number of the returned medicine/placebo packages.

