### Statistical analysis

The proportion of patients with at least a four-point change in ADAS-cog and MMSE and the scores on C-DAD will be compared between the active treatment and placebo groups using the Chi-Squared test and independent sample t test, respectively. Missing data will be input using the last-observation-carried-forward (LOFC) approach. All patients randomized with at least one post-randomization measurement will be included in the primary analysis to follow the intention-to-treat principle. Analyses will be done with SPSS 19.0 package (SPSS, Chicago, IL).

To get a more comprehensive picture of the efficacy of DTD, a post-hoc analysis of the differences in the change of ADAS-cog and C-DAD sub-scores of the active treatment group will be compared between the active and placebo groups. To reduce the number of statistical comparisons, analyses will be performed with a hierarchical approach. To begin, the scores of ADAS-cog at week 24 (end of treatment) for the active treatment and placebo groups will be compared. If the difference is deemed statistically significant at a 2-sided *α*-level of 0.05, the scores of ADAS-cog at week 12 (half of treatment) and week 30 (end of observation period, that is, without treatment) will be compared between groups. C-DAD will be analyzed in the same manner as ADAS-cog.

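### Week-24 ADAS-cog and C-DAD totals are compared with no stated baseline adjustment, and the C-MMSE total, a declared secondary outcome, is tested only as a four-point-change proportion

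*Protocol article*

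**What the plan says.** The section on the primary outcome makes an ADAS-cog responder rate (at least four points) primary and three totals secondary: "Total scores of the ADAD-cog, Chinese version of Mini-Mental State Examination (C-MMSE") and the C-DAD "score [31] will be used as secondary outcomes". On timing it states: "Outcome measurements will be carried out during the study visits at weeks 0, 12 (half of treatment), 24 (end of treatment) and 30". A week-0 value is therefore planned for every scale.

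The Statistical analysis section then fixes the tests. Its first sentence reads "The proportion of patients with at least a four-point change in ADAS-cog and MMSE and the scores on C-DAD will be compared" between the arms, "using the Chi-Squared test and independent sample t test, respectively". The order of that sentence ties the chi-squared test to the ADAS-cog and MMSE proportions and the t test to the C-DAD scores.

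The second paragraph sets up a hierarchy. First, "the scores of ADAS-cog at week 24 (end of treatment) for the active treatment and placebo groups will be compared"; weeks 12 and 30 follow only if that comparison is significant at two-sided 0.05. Then: "C-DAD will be analyzed in the same manner as ADAS-cog". No test, covariate or model is named for the ADAS-cog week-24 step. The same paragraph speaks of change for the ADAS-cog and C-DAD sub-scores, but of scores for the totals.

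The Recruitment procedures section plans at least 40 patients, 20 per arm. On allocation, the protocol says "Group allocation will be simple randomization in a ratio of 1:1". The Discussion says that no sample size calculation applies.

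**The concern.** Two separate things are wrong.

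First, patients with mild to moderate disease will differ in severity at entry, and week-24 totals carry that spread. A comparison of week-24 totals alone leaves it all in the error term, although the week-0 score is available to remove part of it. With about 20 per arm, that precision matters. It matters most for ADAS-cog, because an imprecise first step in the hierarchy also closes the way to the week-12 and week-30 comparisons. The article hopes the trial will inform the size of a full-scale study, and a wide interval around the effect estimate serves that aim poorly.

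Second, the outcome list and the analysis text disagree on C-MMSE. The total is declared, but only a proportion is tested. The declared outcome therefore has no analysis, and cutting a score at a threshold discards information. This loss comes from dichotomisation and is separate from the omission of baseline.

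**Working it through.** **Inputs from the article.** n = 20 per arm; two-sided alpha 0.05; 4 points as the meaningful ADAS-cog change; week-0 scores planned. The article states no power, SD, correlation or effect size, so there is no figure of its own to reproduce.

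**Assumed inputs.** Correlation rho between week-0 and week-24 scores: 0.5 to 0.85. SD of the score: 10, with 8 and 12 as a check. True difference: 4 points.

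**Step 1: variance.** Relative to a raw week-24 comparison (variance 1), ANCOVA has variance 1 − rho² and a change-score comparison has 2(1 − rho). The saving of ANCOVA over change scores is 1 − (1 − rho²)/[2(1 − rho)] = (1 − rho)/2.

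**Step 2: power.** Noncentral t with noncentrality (4/10) × √(20/2) / √(relative variance). For the raw comparison this is 0.4 × 3.162 = 1.265 on 38 df, which gives 23%. For ANCOVA at rho = 0.7 it is 1.265/√0.51 = 1.771 on 37 df, which gives 41%.

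| rho (assumed) | ANCOVA variance | Removed v raw | Removed v change | Power, raw | Power, ANCOVA | Raw-score n per arm equal to 20 with ANCOVA |
|---|---|---|---|---|---|---|
| 0.5 | 0.75 | 25% | 25% | 23% | 30% | 27 |
| 0.6 | 0.64 | 36% | 20% | 23% | 34% | 31 |
| 0.7 | 0.51 | 49% | 15% | 23% | 41% | 39 |
| 0.8 | 0.36 | 64% | 10% | 23% | 54% | 56 |
| 0.85 | 0.28 | 72% | 7.5% | 23% | 65% | 72 |

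The last column is 20/(1 − rho²).

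**Step 3: sensitivity.** Estimating the slope inflates the ANCOVA variance by about 1 + 1/(2 × 20 − 4) = 1.028, which lowers the ANCOVA power by about 1 percentage point. With SD 8, raw power is 34% and ANCOVA 43% to 83%; with SD 12, 18% and 22% to 50% (rho 0.5 to 0.85). ANCOVA is better at every correlation shown, so the recommendation does not depend on where in the range the truth lies; only its size does.

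**Step 4: the C-MMSE cut.** The efficiency of a proportion relative to the mean of a normal variable cut c SDs from its mean is φ(c)²/[p(1 − p)], where p is the tail beyond the cut. The loss is 36% at c = 0, 56% at c = 1 and 73% at c = 1.5. The article does not allow c to be fixed for C-MMSE, so this is a range. It must not be combined with the 1 − rho² figures.

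**The case against.** Several objections have force.

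*The size is not in the document.* This is correct. Any single headline loss would rest on an assumed correlation. Quoting only half to nearly three quarters, for example, takes rho of 0.70 to 0.85 as known. Mild-to-moderate eligibility and last-observation-carried-forward leave rho uncertain, so the wider range is the honest one.

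*Scores could mean change scores.* The hierarchy sits in the paragraph that opens with changes in sub-scores, so this reading is plausible. It shrinks the gain over ANCOVA to 25% at rho 0.5 and 7.5% at rho 0.85. The literal wording favours raw totals, because the paragraph uses change for one and scores for the other, but the text does not settle it.

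*The t test is named only for C-DAD.* This is true; for the ADAS-cog totals it is an inference, since no other test for a continuous score appears.

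*An article condenses.* Covariates for secondary outcomes may be left to a fuller document. But this article does state its tests, time points and order of testing, and the point concerns those stated choices. The C-MMSE mismatch lies between two of its own sections.

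A reader might also infer more than the article supports:

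- That the baseline scores go unused altogether. They do not: the ADAS-cog and MMSE four-point outcomes and the sub-score comparison are changes and need week 0.
- That simple randomisation makes the unadjusted comparison biased. It does not. The comparison is unbiased over randomisations and its standard error already covers chance imbalance, so imbalance is the same imprecision seen from another side.
- That ANCOVA would sharpen the SD estimate for planning. Residual degrees of freedom are 38 without it and 37 with it, so it would not, and the change SD and the correlation can be computed from the same data whatever test is used. The gain is in the effect estimate.

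**Conclusion.** The point holds in limited form. As worded, the week-24 ADAS-cog and C-DAD total comparisons make no use of the week-0 score. If raw scores are meant, this forgoes about 25% to 72% of the variance for an assumed rho of 0.5 to 0.85; in power terms, about 23% against 30% to 65% for a 4-point difference, SD 10 and 20 per arm. If change scores are meant, the variance forgone is about 25% to 7.5%. The direction is secure, while the size is conditional on values that the article does not give.

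The C-MMSE inconsistency needs no assumption: the total is declared as an outcome and only a four-point proportion is tested.

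The primary responder outcome is not touched by this point. It concerns secondary analyses and is worth correcting without threatening the trial's validity.

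**What to change.** - Analyse the week-24 ADAS-cog, C-DAD and C-MMSE totals by ANCOVA, with the week-0 score of the same scale as covariate. A baseline-adjusted repeated-measures model over weeks 12, 24 and 30 would also serve.
- Report each adjusted difference with its 95% confidence interval.
- Let the C-MMSE total model replace the MMSE four-point chi-squared test, so that the declared outcome has its analysis.
- Keep the ADAS-cog responder rate as primary.
- State plainly that the hierarchy's week-24 comparison is this baseline-adjusted one, which removes the doubt over raw or change scores.

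The cost is one degree of freedom per ANCOVA model and a change of wording. The week-0 data are already scheduled, so nothing new need be collected. The article keeps allocation masked until the end of the study and plans no interim analysis, so the change can be made and dated before unblinding. The article requires ethics approval for any protocol amendment.

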### Compliance strategy

This will be a 30-week clinical trial, in which subjects will need to take study medication for 24 weeks with 8 regular visits (week 0, 4, 8, 12, 16, 20, 24 and 30). In order to maximize subjects’ compliance, first, we will have a thorough consent process for all participants; we will explain in detail the study schedule, potential side effects of treatment, and the responsibilities of the subjects. Second, we will screen potential subjects carefully during a 2-week run-in period in order to exclude ineligible patients or patients who are unlikely to comply with treatment regimen before randomization. Third, we will try to prevent dropouts by providing ongoing support to patients. A special e-mail account and a direct telephone line set up for this clinical trial will enable the study team to personally communicate with the patients. An information sheet will be given to each participant providing them and their caregivers with means of urgent contact. Extra visits and free medical care will be arranged for any participant who feels harmed by the trial protocol. Fourth, this is an add-on design [32], which means that the study treatment is added to their existing treatment. Certainly those participants receiving the placebo should not experience any difference in their condition, while those receiving the DTD should improve or at least remain the same.

### Early termination

The trial will be terminated for a specific participant in the event of any of the following: (1) participant develops severe adverse side effect(s); (2) participant shows hypersensitivity towards DTD; (3) participant develops some other life-threatening condition or disease; or (4) participant chooses to participate in another Chinese medicine research project. In addition, any participant may voluntarily withdraw.

The whole research plan will be terminated under the following circumstances: (1) presence of serious adverse effect(s) related to Chinese herbal medicine with supportive evidence or (2) completion of all follow-up assessments.

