### Study medication

The herbal medicine under study is DTD (Table 1). It is composed of Arisaema Cum Bile (DanNanXing in Chinese), Pinelliae Rhizoma (FaBanXia in Chinese), Aurantii Immaturus Fructus (ZhiShi in Chinese), Poria (FuLing in Chinese), Citri Reticulatae Pericarpium (ChenPi in Chinese), Acori Tatarinowii Rhizoma (ShiChangPu in Chinese), Ginseng Radix (RenShen in Chinese), Bambusae in Taeniam Caulis (ZhuRu in Chinese), Glycyrrhizae Radix (GanCao in Chinese), Zingiberis Recens Rhizoma (ShengJiang in Chinese) and dextin [13]. The test report of the DTD quality control is attached in the Additional file 3. The placebo is made of caramel (2%), gardenia yellow pigment (0.05%), sunset yellow (0.02%), tartrazine (0.02%), dextrin (95%) and broadleaf holly leaf (2.91%) [25]. The granules were produced in a single batch (DTD batch no.: A12074 Placebo batch no.: A120817) strictly in compliance with standards of Good Manufactory Practice (GMP) and Chinese Pharmacopoeia 2010 to ensure the stability and homogeneity of the composition as produced by PuraPharm Pharmaceuticals Company Limited. The chemical compositions of the final products were analyzed for contamination with heavy metals, toxic elements, microbe and pesticide residues; both final products were analyzed for stability and adherence to quality standards. The active treatment granules and the placebo granules have identical appearance and smell, and both have been packed in sealed opaque aluminum sachets and put in zip lock bags (10 sachets each). Only the treatment code is printed on the package to ensure successful blinding of patients [26]. One sachet contains 13.5 g, a dosage equivalent to 67.5 g herbs. All herbal and placebo granules will be distributed by [name] with both written and verbal instructions for each participant. Patients will be instructed to take the granules orally by dissolving a sachet of granules in 150 ml hot water, stirring well, then drinking the solution, two times per day, at least two hours apart from taking any routine Western medication. Patients will be allowed to discontinue the study granules temporarily if any adverse events occur. Patients will be instructed to report such events to a special e-mail account or by a direct telephone line. Additional treatments for a newly occurring illness, for example, flu or diarrhea, or adverse event during the study will be allowed but must be reported to the assessor.

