### Recruitment procedures

Three methods will be used to recruit participants with AD. The first source of candidates will be referral from two public Western medicine hospitals in Hong Kong (Prince of Wales Hospital and Queen Elizabeth Hospital) from our co-investigator (Co-I), [name], and our research teammate, [name]. The second source will be referral from the Chinese medicine clinic of Hong Kong Baptist University. A third source of candidates will be those who respond to advertisements published in local newspapers and newsletters of local AD societies.

Figure 1 shows the schedule of enrollment. We plan to recruit at least 40 patients, which will allow 20 for the DTD group and 20 for the placebo group in this study. All patients diagnosed with AD will be referred to a Chinese medicine doctor who is the Principle Investigator of the study ([name]), or to a Research Assistant ([name]), for further assessment and recruitment. The aim, procedures, nature of study and possible side effects of DTD will be explained by the PI or RA; then, each subject will be asked to sign a written consent [see Additional file 4] to take part in the study. Patients will be informed that they are free to withdraw at any time during the study.

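### The early termination rule ends the trial, not only the study granules, for participants with severe side effects, hypersensitivity or a life-threatening condition; read naturally, it also ends their outcome assessments

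*Protocol article*

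**What the plan says.** All references are to the protocol article.

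- **Early termination, participant level.** "The trial will be terminated for a specific participant in the event of any of the following: (1) participant develops severe adverse side effect(s". The second condition is "participant shows hypersensitivity towards DTD". The third is some other life-threatening illness. The fourth is "participant chooses to participate in another Chinese medicine research project". Voluntary withdrawal is added directly after the list.
- **Early termination, whole study.** The same verb is used for the research plan, which is terminated, among other grounds, on "completion of all follow-up assessments".
- **Study medication.** Stopping the granules alone is mentioned once, as a temporary measure: "Patients will be allowed to discontinue the study granules temporarily if any adverse events occur".
- **Primary outcome and its assessment.** "Outcome measurements will be carried out during the study visits at weeks 0, 12 (half of treatment), 24 (end of treatment) and 30". Adverse events, vital signs and physical examination are covered throughout the study, and "laboratory safety screening of liver and renal function will be performed at week 24".
- **Statistical analysis.** The primary analysis takes randomized patients who have any measurement after randomization, and describes this as following intention-to-treat. Missing values are filled by last observation carried forward (LOCF).
- **Compliance strategy.** Regular visits are also planned at weeks 4, 8, 16 and 20. Extra visits and free care are offered to participants who feel harmed.
- **Recruitment procedures.** The plan is "20 for the DTD group and 20 for the placebo group".

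**The concern.** An intention-to-treat comparison needs outcomes from participants who stop treatment as well as from those who continue. If stopping the granules for a severe reaction also takes the participant out of the trial, the protocol itself creates missing outcomes, and the reason for them is how the participant tolerated the treatment or how ill the participant became. Such missingness may be informative, and it is avoidable: a participant who can no longer take the granules can often still be assessed.

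At stake are the week-12, week-24 and week-30 values of these participants. The analysis rules would then either drop the participant or substitute an older score. In a pilot of about 20 per arm, meant to inform the size of a later trial, a few such cases carry weight.

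**Working it through.** The article gives no termination rate, response rate or effect size, so there is no stated figure to reproduce. The check is a reading of the text followed by counting.

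**1. What is terminated?** Three features point to exit from the trial rather than from dosing:
- the object of the sentence is the trial;
- the fourth condition (joining another project) and the adjoining voluntary withdrawal concern participation, not dosing;
- Study medication names the granules when only dosing is meant, and there the stop is temporary.

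No section describes a permanent stop of the granules with continued scheduled assessment. No section forbids it either.

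**2. Assessments lost on that reading.** Post-baseline outcome times are weeks 12, 24 and 30, so three in all.

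| Terminated | Lost | Left for analysis |
|---|---|---|
| before week 12 | 3 of 3 | baseline only |
| between weeks 12 and 24 | 2 of 3 | week 12 |
| between weeks 24 and 30 | 1 of 3 | weeks 12 and 24 |

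The first window covers 12/24 = 50% of the treatment weeks. This is a share of time, not a probability of exit. The visits at weeks 4 and 8 do not help, because no outcome measurement is placed there.

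**3. How the analysis rules treat these participants.**
- *Before week 12.* If *measurement* in the inclusion rule means an outcome measurement, the participant is excluded from the primary analysis. If a vital sign or other safety reading counts, the participant stays in and LOCF can only carry baseline forward. The change is then 0, below the four-point threshold, and the participant counts as a non-responder. The article does not say which applies.
- *Between weeks 12 and 24.* The week-12 score stands in at week 24, the time point that opens the hierarchical comparison, and at week 30.

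**4. What is left unknown per arm.** Let k participants of a planned arm of 20 have no outcome, and let r of the rest be responders. With everyone assessed, the arm's proportion would lie between r/20 and (r + k)/20, a width of k/20:
- k = 1: 1/20 = 5 points
- k = 2: 2/20 = 10 points
- k = 3: 3/20 = 15 points

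The values of k are assumptions. The width is a best-case to worst-case range, not an expected bias.

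**5. Can a direction be derived?** Assume, for illustration only, 8/20 responders on DTD and 3/20 on placebo if all were assessed: 40.0 − 15.0 = 25.0 points. Let two DTD participants be terminated before week 12.

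| Handling | Both would be non-responders | Both would be responders |
|---|---|---|
| excluded | 8/18 − 3/20 = 44.4 − 15.0 = 29.4 | 6/18 − 3/20 = 33.3 − 15.0 = 18.3 |
| baseline carried forward | 8/20 − 3/20 = 25.0 | 6/20 − 3/20 = 15.0 |

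The estimate can move up, down or not at all, depending on facts the article does not give.

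**The case against.** **The loss of assessments is inferred.** The section says when the trial ends for a participant, not what is recorded afterwards, and a condensed article may leave that to the full protocol. The prose is also loosely edited elsewhere, so *the trial* may have been shorthand for trial treatment. This stands as a limit. It does not dispose of the point, because the article states a rule and the rule as written ends the trial. If shorthand was meant, the same rewording removes the doubt. A reader might infer that the protocol forbids later assessment; no sentence does.

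**Exclusion is conditional.** A reader might infer that everyone terminated before week 12 leaves the primary analysis. That holds only if *measurement* means an outcome measurement, which the article does not state.

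**The mechanism lies partly elsewhere.** The analysis-set rule and LOCF produce the effect, and they apply equally to voluntary withdrawals. This is correct. Changing the termination rule removes only the part that the protocol itself imposes.

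**A bias in favour of DTD is not shown.** A reader might infer one, since true hypersensitivity to DTD can arise only in the active arm. Under blinding, however, a suspected case can occur in either arm, and severe side effects are not confined to one. With the assumed 8/20 versus 3/20, removing two DTD non-responders takes the uncorrected chi-squared p-value from 0.077 to 0.046, but only because every exit was placed among DTD non-responders. The documents support neither the counts nor the placement.

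**Part of the problem is already handled.** Temporary stopping of the granules is allowed for any adverse event, so only the more serious cases trigger the rule. Safety data up to termination are kept, and care is offered to those harmed. Both facts reduce the expected number of cases or their consequences; neither restores the scheduled outcome assessments.

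**Conclusion.** The point holds as a low-to-moderate matter. The rule ends the trial for participants with severe side effects, hypersensitivity or another life-threatening condition. On its natural reading it costs 3 of 3 post-baseline outcomes before week 12, and 2 of 3 between weeks 12 and 24. The counts follow from the article's own schedule.

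The conclusion rests on two assumptions: that *the trial* means participation, and that the full protocol does not provide otherwise. Whether a participant terminated before week 12 is excluded or has baseline carried forward depends on an undefined term. The 5 to 15 points depend on an assumed 1 to 3 participants in an arm of 20. Neither the size nor the direction of any bias can be derived.

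**What to change.** Keep the clinical stopping conditions, but change what they stop. Reword conditions (1), (2) and, where clinically feasible, (3) so that they end the study granules only. State that the scheduled week 12, 24 and 30 assessments continue unless consent is withdrawn.

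Two small additions are optional. In condition (2), refer to the study granules instead of DTD, since treatment is blinded. For a participant who stops early, draw the planned liver and renal panel at the stopping visit: after a stop at week 4 or week 20, the week-24 panel would come 24 − 4 = 20 or 24 − 20 = 4 weeks after the last dose.

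The cost is a protocol amendment, for which the Study design section requires renewed ethics approval, and some effort to retain participants who have stopped the granules. No visit is added to the existing schedule, although participants who would otherwise have left would attend up to three more assessments. The gain is limited: Trial status reports 36 subjects enrolled of at least 40 planned, so the change helps only those still to be enrolled or still in follow-up.
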